## Abstract

**Introduction:** The prevention of schizophrenia and other psychotic disorders has led researchers to focus on early identification of individuals at clinical high risk (CHR) for psychosis and to treat the at-risk symptoms in the pre-psychotic period. Although at-risk symptoms such as attenuated hallucinations or delusions are common in adolescents and associated with a marked reduction in global functioning, the evidence base of effective interventions for adolescents at CHR state and even ﬁrst-episode psychosis is limited. Thus, the present protocol describes a study design that combines therapy modules for CHR adolescents with a smartphone application supporting the young individuals between the therapy sessions. The treatment approach “Robin” is based on existing therapy strategies for adolescents with first episode of psychosis and the available recommendations for adults with at-risk symptoms.

**Methods:** The evaluation aims firstly to compare the efficacy of Robin in 30 CHR adolescents aged 14–18 to an active control group (treatment as usual) from a previous study. Primary outcome measures will be at-risk symptomatology, comorbid diagnosis, functioning, self-efficacy, and quality of life. For the prospective intervention condition (16 weekly individual sessions + a minimum 4 family sessions), help-seeking adolescents with CHR for psychosis, aged 14–18, will be recruited over 3 years. At-risk and comorbid symptoms, functioning, self-efficacy, and quality of life are monitored at six time points (baseline, during the treatment period; immediately after intervention; and 6, 12, and 24 months later) and compared with the respective measures of the active control group.

**Discussion:** To the best of our knowledge, this is the first controlled trial to test the efficacy of a specific early psychosis treatment in combination with a smartphone application for adolescents at CHR for developing psychosis. The results of the study are expected to add information that may substantially decrease the burden of CHR adolescents and increase their resilience. It may offer age-adapted and targeted strategies to guide clinicians in the treatment of these vulnerable individuals. Furthermore, research in the field of early intervention will be enriched by our findings.

**Clinical Trial Registration:**
www.ClinicalTrials.gov, identifier NCT03829527.

## Introduction

Psychotic disorders are severe mental illnesses that typically emerge in late adolescence or early adulthood (1). The disorders lead to considerable social and economic deficits, as well as burden for the individual and family (2). Prior to the onset of the first psychotic episode, the majority of the individuals experience attenuated psychotic symptoms, known as at-risk symptoms (3).

Two different sets of clinical high risk (CHR) criteria have been developed for the purpose of early identification of individuals at CHR: 1) the basic symptom criteria focusing on subtle, subjectively experienced changes in cognition and perception and 2) the ultra-high-risk criteria, such as attenuated positive symptoms indicating the imminent manifestation of psychosis (4). In the present article, we use the term CHR state, which includes both of these current risk concepts.

There is an ongoing discussion as to whether or not to treat at-risk symptoms (5–7). The rates of CHR individuals transitioning to psychotic disorders have declined over the years of early detection research (8), and the specificity of at-risk symptoms is questioned (5, 9). At-risk symptoms are common in the general population, particularly during adolescence; it is a clinical challenge as to how to differentiate between young people who are at risk and those who are not (10, 11). Nevertheless, leading experts in the field of early intervention in psychosis have claimed that treatment of at-risk symptoms in the help-seeking population is justified independently of the risk of conversion to psychosis [for example, Refs. (12–15)].

CHR individuals and their caregivers report high levels of distress due to these symptoms (16). The CHR state is associated with suicidality, impairments to global functioning, and a decline in quality of life (17–23). CHR individuals report poorer social relationships and higher rates of loneliness than do healthy peers (24). Furthermore, CHR individuals seem to have poor coping skills, low levels of self-efficacy, and negative metacognitive belief similar to that seen in patients with depression or with a frank psychosis (25–27). Recent studies have shown a high prevalence of psychiatric comorbidities in CHR populations for psychosis (28, 29), especially in younger CHR individuals (20). Moreover, the CHR state is associated with long-term implications, independent of conversion to psychosis. A recent study showed that about half of non-transitioned CHR individuals remained functionally impaired and presented with at least one comorbid disorder at a 6-year follow-up (30). On the other hand, CHR individuals who convert to psychosis have shown poorer clinical outcomes than do first episode psychosis patients without a history of at-risk symptoms (31). Consequently, current data clearly favor targeting and treating at-risk symptoms in help-seeking individuals.

Although at-risk symptoms are common in adolescents and associated with a marked reduction in functioning in this age group (23), the evidence base required to guide effective interventions for CHR adolescents and even ﬁrst-episode psychosis is limited (15, 32–35). Most intervention studies in the CHR population have included adult patients, with only a few including younger patients (36–40). A majority of them used the same treatment approaches for adults and adolescents. Consequently, there is a lack of investigation targeting age-appropriate treatment strategies in this vulnerable age group. The transition from childhood to adulthood is a very complex developmental stage, and age-adapted intervention strategies are required. The CHR state can disrupt social and psychological development, such as the achievement of educational goals or the construction of peer relationships. Therefore, minor CHR individuals need treatment strategies that address the complex symptomatology, the associated burden, and their reduced functioning. Furthermore, when focusing on engagement in therapy during first psychotic episodes, the data demonstrated that age-appropriate treatment approaches drawing from youth specific interests are needed to address and involve the younger patients (32, 41).

To fill this gap, the experts from the specialized outpatient care unit for early intervention in psychosis at the Department of Child and Adolescent Psychiatry and Psychotherapy, Psychiatric University Hospital of the University of Zurich (CAPS), developed the specialized treatment approach “Robin” for CHR adolescents. The treatment program Robin is an integrated psychotherapeutic approach. Robin comprises individual therapy, family sessions, and a smartphone application for supporting patients between sessions. The therapy modules are based on treatment strategies in CHR adults (6, 14, 42–44) and recommendations for adolescents with first episodes of psychosis (33, 45, 46). It follows the guidance on early intervention in CHR states of psychosis of the European Psychiatric Association (EPA) (15).

The treatment modules are also based on existing concepts of cognitive behavioral therapy (CBT). CBT is currently the most widely approved psychological intervention in early intervention of psychosis and recommended by EPA guidance (15). Previous studies showed that CBT may prevent or at least postpone a first psychotic episode in CHR individuals (47); however, these promising findings need replication, and studies applying CBT in adolescents are rare. Cognitive remediation is used as a supplement treatment and focuses on improving cognitive and social skills. Additionally, the treatment modules comprise aspects of systemic therapy, which have been found to be efficacious in the treatment of psychosis in adult patients (48). Assuming that family environment plays a more relevant role in adolescents than in adults, there is a strong rationale for the possible benefits of systemic intervention in adolescents with CHR state. The initial studies of systemic treatment approaches in adolescents with psychosis (32) and CHR adolescents are promising (36, 39).

In addition to the above, the intervention also includes the smartphone application “Robin Z.” Smartphones have become everyday devices, and most people use them in their daily routine. Previous analyses showed that for young people, in particular “digital natives,” it may be helpful to develop technology-based treatment approaches as a way of connecting with them about mental health issues (49–51). There is increasing interest in using mobile technologies such as smartphone applications in mental health care (52–54). Primarily, mobile technologies were utilized to collect research data. These technologies allow for real-time assessment. This provides more accurate data about real-world contexts in which experiences are made or behaviors occur (55, 56). So risk and protective factors in the psychosocial environment and their impact on mental health can be more easily identified. Further, studies with smartphone assessments showed higher engagement in completing all examinations and lower dropout rates than did studies with paper-and-pencil assessments (57, 58). Recently, research projects have examined feasibility and validity of mobile technologies in supporting therapy (53, 59). Smartphone interventions have many advantages like accessibility, portability, 24-h support, or real-time intervention. Using smartphones in everyday situations (i.e., on the bus, at school, and on the street) is routine, and so interventions *via* smartphone are not likely to be stigmatizing (49). The problem of recall bias in retrospective reports can be reduced or avoided. This helps the psychotherapist to give more tailored feedback to support and reinforce changes in the patients’ behavior according to their psychological health. Furthermore, self-monitoring also provides advantages for the patients themselves. The repeated measurement of their symptoms and mood can reveal insights into their psychological processes (60). Reid and colleagues (61) found an increased self-awareness regarding their symptoms and mood after using a symptom-monitoring smartphone application in a group of younger psychiatric patients. There is also evidence that medication adherence can be improved through smartphone intervention (62, 63).

In the treatment of psychotic disorders, the first research results from the use of smartphone applications are promising (62, 64–68); however, there is little known about mobile technologies addressing at-risk symptoms (50). Despite current analysis demonstrating young people would be interested in using mobile technologies, there is a lack of investigations with this population (49, 51). The available studies have shown a high acceptance and subjective satisfaction with mobile interventions in young people with psychiatric problems (57, 61, 69).

There is great heterogeneity across symptomology and functioning in the CHR population (30, 70). As a consequence, individualized adaptive treatment approaches are required. While some individuals will respond to an intervention, others will not. Robin is an individually tailored approach, and the treatment is personalized to the individuals’ special needs depending on their stage of illness, presence of comorbidities, or functional impairment.

The current clinical trial “Evaluation of the Treatment program Robin” (ETRo) has two main study goals:

to investigate the feasibility and impact of the combined treatment program: the structured therapy and the smartphone application; andto investigate the efficacy of this specific intervention versus treatment as usual (TAU).

Hypotheses of the study:

Hypothesis 1: Robin is feasible and accepted in this young population of CHR individuals. The adolescents will show high treatment engagement.Hypothesis 2: Robin improves the quality of life and self-efficacy at 6-, 12-, and 24‐month follow-up in individuals with CHR compared with individuals with CHR who received TAU.Hypothesis 3: Robin enhances the rate of adolescents with clinical and psychosocial functional remission at 6-, 12-, and 24‐month follow-up than does TAU.

## Methods and Study Design

The ETRo Trial is a prospective, single-center, follow-up study comparing a specific treatment program for adolescents with at-risk symptoms with a sample from a previous study having received TAU.

### Participants

Participant recruitment will run between September 2017 and continue until September 2020 in the early recognition center for psychosis of the Department of Child and Adolescent Psychiatry and Psychotherapy, Psychiatric University Hospital of the University of Zurich (CAPS). The ETRo trial is a naturalistic treatment study. All participants will be help-seeking adolescents (aged 14–18) with at-risk symptoms assessed at the early recognition center. The purpose of the study, the study process, risks, benefits, and alternatives will be explained to all participants and their caregivers according to ethical principles. All participants will be asked to give a written informed consent in accordance with the national law. For inclusion, participants must meet at least one of the following at-risk criteria: 1) at least two self-experienced and self-reported cognitive basic symptoms as assessed by the Schizophrenia Proneness Interview Child and Youth Version (SPI-CY) (71) and/or 2) at least one attenuated psychotic symptom for psychosis assessed by the Structured Interview for Prodromal Syndromes (SIPS) (72).

Exclusion criteria for study participation include a diagnosis of a psychotic disorder, current substance or alcohol dependence, aged below 14, insufficient German or English language ability, or low intellectual abilities with IQ < 75.

### Study Design

Within this prospective evaluation data for at-risk symptoms and comorbid symptoms, global functioning, self-efficacy, and quality of life will be collected at six time points (baseline, during the treatment period; immediately after intervention; and 6, 12, and 24 months later). The treatment period will be 16 weekly, individual sessions combined with at least four family sessions starting after the baseline clinical assessment (**Figure 1**).

**Figure 1 f1:**
[figure not shown]
Flow chart of the assessments from baseline to 24 months of follow-up.

##### App Robin Z

The app Robin Z (**Figure 2**) was developed to enrich the treatment sessions. A modular version of the app was developed and modified after the first pilot investigations with patients (*N* = 7, aged 14–18) and clinicians from the CAPS (*N* = 10). All clinicians within the pilot study reported that they would like to use the app Robin Z to enrich their therapeutic approaches. All patients in the pilot project used the app in their daily lives. Modules containing information about symptoms and coping strategies were used most frequently by patients. The findings were used to improve and adapt the application. In September 2017, the development of Robin Z was finalized and published on iTunes and Google Play. The technical aspects of Robin Z are regularly maintained without changes to the content.

**Figure 2 f2:**
[figure not shown]
Example screenshots of the app Robin Z.

The app is developed as an adjunct to the therapy and not a replacement for appropriate medical treatment and management. It is not at treatment itself, and it is not seen as a medical product according to the Swiss Medical Devices Ordinance Act. The authors recommend using the app in combination with a psychological treatment. Furthermore, it may be a used after completion of the study and/or therapy.

The app works offline and is not connected to the internet. Data collected by the app are stored in a private directory. These data are protected by the operating system and are inaccessible to other software on the device. The app does not transfer or store any data on the internet, and no data are stored outside of its private directory. In addition, the app is also password protected.

The app contains the following features:

**Symptom management:** Users will receive information about their symptoms and suggestions for managing them *via* the app. In therapy, these coping strategies are discussed with the patient and, if necessary, explained by the clinician. The adolescents can also define their own coping strategies and note helpful thoughts under the function “Memo.” The adolescents will be asked about their symptoms and their mood several times a day. They agree together with their therapists how many prompts they will receive each day. The symptom records are saved under a “Logbook.”

**Medication:** The individuals can record their medication, and they can set up a reminder. Medication adherence can be monitored through the Logbook.

**Crisis intervention:** In collaboration with their therapists, adolescents can set up a crisis intervention plan including emergency contacts. They can call the emergency contact directly *via* the app.

**Weekly goals:** The individuals can set their own goals. This means small, attainable goals so that they experience success. Furthermore, they are supported when dealing with their daily challenges. The goals are decided in the therapy session.

**Library:** The “Library” offers positive reinforcement for dealing with daily life. It consists of a list of strengths and positive experiences. The lists of strengths and positive experiences are discussed and extended on every week in therapy. There are suggestions for positive activities that the adolescents can engage in daily. The individuals are encouraged to do at least one positive activity per day. The suggestions are split into the following categories:

RewardCreative activitiesMovementSocial interactionCognitive trainingWellnessRelaxation exercises

#### Standard Care

The control condition is composed of a control group from a former early recognition study in Zurich (ZInEP) [e.g., Ref. (73)]. The control group consists of 62 adolescents meeting CHR criteria (25 female, age range 13–18 years, mean age 15.06) who historically signed a declaration of consent regarding the use of their data. The sample was accrued from April 2010 to July 2012. The individuals of this subsample of the ZInEP had been treated with non-standardized psychological intervention (TAU) also at the CAPS. Within the ZInEP study, the comparable primary and secondary outcomes (at-risk symptoms, comorbid symptoms, global functioning, self-efficacy, and quality of life) have been evaluated at the same time points (at baseline and 6, 12, 24, and 36 months later). Since we expect a high interindividual variability of symptom fluctuation, reduction, or progression during the phase of intervention, we plan to reduce further putative impact of sex and age and to match individuals from the intervention group to ZInEP individuals accordingly. Consequently, 30 individuals from the ZInEP sample will be included in the statistical analysis.

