### Clinical Analyses

Differences in the primary and secondary outcomes between the two study groups at all time points will be examined with repeated measures analysis of variance and standardized effect sizes (Cohen’s *d*) will be reported. Their respective confidence intervals will be calculated for comparison. Response and remission rates will be compared across groups with contingency tables and differences tested with χ^2^. All unidirectional hypotheses will be tested one sided; bidirectional hypotheses will be tested two sided. Alpha is set to *p* < 0.05. All analyses will be conducted within SPSS.

A linear mixed model approach will be used to assess differences in the primary and secondary outcomes between the two study groups. Logistic regression will be used to assess response and remission rates across the groups. Medication, education, and intelligence will be taken into account as confounding factors by including them in mixed model and logistic regression model, respectively. All unidirectional hypotheses will be tested one sided; bidirectional hypotheses will be tested two sided. Significance level α is set to 0.05.

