## Discussion

Despite evidence suggesting that young individuals with at-risk symptoms may profit best from specialized treatment approaches (85), little is known about age-appropriate treatment strategies in this vulnerable age group (15). The treatment program Robin has been developed to fill this gap.

Our treatment approach Robin is an integrated approach based not only on CBT but also on systemic therapy. The treatment is both solution and resource focused. Furthermore, Robin is an individualized treatment approach in line with the individual needs of the particular patients, which should lead to a high acceptance. Furthermore, age-appropriated treatment material, including a smartphone app and the involvement of the family, may result in higher engagement in therapy (32, 41, 49). The smartphone application Robin Z has been developed to enrich the treatment and to increase treatment satisfaction through providing support between sessions. Previous studies have already demonstrated that mobile-based interventions are feasible and accepted by psychotic patients (49, 58, 59, 66); thus, we expect the same for CHR individuals.

In accordance with EPA guidance in early intervention in CHR states of psychoses (15), a primary aim of this treatment approach is to improve the daily functioning. Thus, the study group decided to primarily focus on quality of life, self-efficacy, and functioning. These areas have been shown to be most impacted in adolescents and often prompt them to seek help (18, 30, 44, 86, 87). In contrast, at-risk symptoms are not necessarily the cause of the highest psychological strain and burden for the patient. Furthermore, we expect a remission or at least a significant decline of the at-risk symptoms in most patients after the treatment period. Prior evidence has demonstrated that at-risk symptoms, especially in adolescents, show high levels of fluctuation (70, 88). How much this fluctuation symptoms or remission rates are associated with a specific intervention is currently unknown. Our first analysis of symptomatology in the control group also showed a high reduction of at-risk symptoms during follow-up compared with the baseline.

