Using a control group of our previous early recognition study ZInEP and a non‐randomized design could be possible sources of bias. However, data of the control group participants of ZInEP were reassessed at the same time points (6, 12, and 24 months), and identical measures were used. The TAU was carried out in the same outpatient service under the supervision of [name] There were no major changes in the Swiss health system between 2010 and 2018 that could have had an influence on the frequency or intensity of therapeutic sessions. The outpatient mental healthcare system in Zurich has remained widely unchanged since then. Another limitation of the control group may be the naturalistic setting. As their treatment was not standardized, many treatment variables, such as the treatment approach or the therapists themselves, cannot be controlled for. However, even though a moderate sample size may limit statistical controlling, important confounders such as effect of medication, hospitalization, and treatment frequency may be identified in both groups and controlled for. Our control group is an extensively and carefully assessed large sample of CHR adolescents (*N* = 62) in the same age range and from the same geographical area. The sample is double that of the intervention sample and allows for age and sex matching to individuals in the intervention study. Consequently, more resources can be allocated to recruiting the experimental group, and therefore, the chance of achieving a larger sample will be increased. This will also help to reduce ethical concerns, as the help-seeking patients will be reporting a high level of distress and requesting a specific treatment. The treatment is based on the current research results in the field of early intervention and prevention of psychosis, as well on the clinical expert knowledge from the therapists in the early intervention center. Therefore, our study team will act on the assumption that the treatment approach Robin will lead to the best possible outcome.

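### Matching uses only sex and age, and no model is stated to adjust for the baseline value of the outcome, so a difference in starting severity can bias the historical-control comparison

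*Protocol article*

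**What the plan says.** All references are to the Protocol article.

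- **Design.** The Discussion names as possible sources of bias the lack of randomisation and "Using a control group of our previous early recognition study ZInEP". Controls were accrued from April 2010 to July 2012 (Standard Care). Robin recruits from September 2017 to September 2020 (Participants).
- **Matching.** Standard Care: "we plan to reduce further putative impact of sex and age and to match individuals from the intervention group to ZInEP individuals accordingly". Thirty of the 62 controls are then analysed. The Discussion repeats that the larger control sample "allows for age and sex matching to individuals in the intervention study".
- **Covariates.** Clinical Analyses: "Medication, education, and intelligence will be taken into account as confounding factors by including them in mixed model and logistic regression model, respectively". The Discussion adds, conditionally, that "important confounders such as effect of medication, hospitalization, and treatment frequency may be identified in both groups and controlled for".
- **Models.** Differences "between the two study groups at all time points will be examined with repeated measures analysis of variance". The same section also plans a linear mixed model, with logistic regression for response and remission. Primary Outcome defines most primary measures as changes.
- **Course of symptoms.** Discussion: "Prior evidence has demonstrated that at-risk symptoms, especially in adolescents, show high levels of fluctuation". It also reports a marked fall in at-risk symptoms from baseline in the controls.

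Baseline symptom severity, baseline functioning and the baseline score of the outcome appear neither among the matching variables nor in either list of confounders.

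**The concern.** Two cohorts recruited about seven years apart, one into an early-recognition study and the other into a structured treatment programme, can differ in how ill they are at entry. Entry is also possible by two routes, basic symptoms or attenuated psychotic symptoms, and the mix may differ. Where scores fluctuate strongly and fell a good deal in controls who never received Robin, starting level is an obvious predictor of later change.

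Standard Care gives the expected variability in symptom course as its reason for matching, yet it matches on sex and age and not on symptom level. Having baseline as one of the repeated measures does not solve this. The group-by-time term is a comparison of changes, and the group main effect averages in the baseline gap itself. At stake is whether a Robin–TAU difference, or the absence of one, can be attributed to treatment.

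**Working it through.** **1. The plan's own figure.** Table 2 gives N per group of 17 (SIPS, 15 points), 16 (SPI-CY, 9 points) and 27 (SWE, 4 points); the GAF row is unreadable. Sample Size states neither SDs nor power, so these numbers can only be inverted. Assuming a two-sided 5% test and 80% power, d = (1.960 + 0.842)×√(2/n):

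| Instrument | n | d (normal) | d (noncentral t) | Implied SD (t) |
|---|---|---|---|---|
| SIPS | 17 | 0.961 | 0.991 | 15.1 |
| SPI-CY | 16 | 0.991 | 1.024 | 8.8 |
| SWE | 27 | 0.762 | 0.777 | 5.15 |

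The implied standardised effects are therefore about 0.78 to 1.02. With a one-sided test at 80% power they would be 0.69 to 0.90.

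**2. Bias with no true treatment effect.** Let D be the baseline difference between groups in SD units and r the baseline–follow-up correlation. Assume equal SDs and that both groups regress towards one common mean. The expected follow-up difference is then r×D.

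- Follow-up-only contrast: bias r×D.
- Change or group-by-time contrast: bias (1−r)×D in size, with the opposite sign.

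D and r are assumptions; the article gives neither. For D = 0.5 SD (about 7.6 SIPS points at the implied SD of 15.1):

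| r | Change contrast | Follow-up contrast |
|---|---|---|
| 0.3 | 0.7×0.5 = 0.35 SD | 0.3×0.5 = 0.15 SD |
| 0.5 | 0.5×0.5 = 0.25 SD | 0.5×0.5 = 0.25 SD |
| 0.6 | 0.4×0.5 = 0.20 SD | 0.6×0.5 = 0.30 SD |

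Relative to Table 2, the smallest value is 0.15/1.02 ≈ 15% and the largest 0.35/0.78 ≈ 45%. On the one-sided reading the range is 0.15/0.90 ≈ 17% to 0.35/0.69 ≈ 51%.

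**3. Effect on the error rate, 30 per group.** The SE of the change contrast is √(2(1−r))×√(2/30), and that of the follow-up contrast is √(2/30) = 0.258. For the change contrast with D = 0.5:

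- r = 0.3: SE 0.306, ratio 0.35/0.306 = 1.14. One-sided rejection in the direction of the bias is Φ(1.14−1.645) ≈ 31%.
- r = 0.6: SE 0.231, ratio 0.20/0.231 = 0.87. One-sided rejection is about 22%.

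The nominal rate is 5%, and Clinical Analyses plans one-sided tests for unidirectional hypotheses. With D = 0.25 and r = 0.3 the rate is about 14%.

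**4. How likely is such a gap?** If both groups were random samples of one population, the baseline difference at 30 per group would exceed 0.25 SD with probability 2×(1−Φ(0.25/0.258)) = 33%, and 0.5 SD with probability about 5%. Historical groups may differ by more than chance, but the article gives no baseline means from which to tell.

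**5. Gain in precision.** A baseline covariate multiplies residual variance by 1−r², which is 0.91 at r = 0.3 and 0.64 at r = 0.6, a reduction of 9–36%. The planned 30 per group is not threatened.

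**The case against.** **Baseline is used.** A reader might infer that the plan ignores baseline altogether. The documents do not support that. The repeated-measures analysis covers all time points, Study Design counts baseline among them, and most primary outcomes are changes. Nor is it right that only sex and age are dealt with, since regression adjustment for three further variables is planned. What stands is narrower: the baseline value is not named as an adjustment variable anywhere.

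**Model detail belongs in a fuller plan.** This is partly fair. The article does not write out the mixed model, and silence is not exclusion. But it fixes the matching variables and names the confounders, and the point is about those stated choices.

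**The bias formula is conditional.** This is correct. If the two cohorts have stable, different means, the change contrast is unbiased and the baseline-adjusted contrast is off by D − r×D = (1−r)×D (Lord's paradox). The data cannot settle which assumption holds. The reported fluctuation and the fall in controls make regression towards a common mean plausible, and showing both contrasts covers the alternative.

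**The design limitation is acknowledged.** The Discussion does acknowledge it. Its defence, however, rests on the same service, time points and measures, which does not address different starting severity.

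**Too many covariates for 60 patients.** This stands against a long list. In a logistic model the rarer outcome class has at most 30 patients; about ten parameters would leave at most 3 per parameter.

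**Conclusion.** The point holds in a limited form. Matching on sex and age, together with adjustment for medication, education and intelligence, leaves baseline severity unadjusted in every stated model, and the logistic models have no stated baseline term. Under a common mean, an assumed 0.5 SD baseline gap and r of 0.3 to 0.6, the resulting bias is 0.15–0.35 SD. That is about 15–45% of the effects implied by Table 2 at an assumed 80% power and two-sided 5% test. These figures are illustrations, not estimates.

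A reader might infer that the bias favours Robin. The documents do not show this. They give no baseline means, and the change and follow-up contrasts are biased in opposite directions. If Robin patients start worse, the change contrast flatters Robin and the follow-up contrast penalises it; if they start milder, both reverse. The fall reported in controls is a within-group observation and says nothing about a between-group gap.

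**What to change.** In Clinical Analyses:

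1. In the mixed model, take the 6-, 12- and 24-month values as the response, these being the follow-up points both groups share. Include the baseline value of the same instrument, and its interaction with time, as covariates.
2. Add one baseline severity covariate to the logistic models for response and remission, and keep the set small. With group, the three named confounders and one severity term, each on one degree of freedom, there are five parameters, so at most 30/5 = 6 patients in the rarer class per parameter.
3. Report standardised baseline differences between the matched groups.
4. Give the change-score contrast as a sensitivity analysis, and say that the two contrasts rest on different assumptions about how the groups would have evolved.

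**Cost.** This changes analysis wording only. Table 1 schedules the instruments at month 0 for Robin, and Standard Care says the comparable outcomes were assessed at baseline in the controls. The price is a few degrees of freedom. Measurement error in the baseline score will leave some residual bias, and adjustment does nothing for unmeasured differences between the cohorts.
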